### Sample size

For the purposes of the current study, we will continue to approach and recruit people until we have randomised 60 participants (20 participants per arm). This should provide us with sufficient information in informing the design of a Phase III RCT. Twelve participants per arm would serve to inform trial feasibility outcomes and provide minimally sufficient precision for preliminary parameter estimates [36, 37]. We will recruit 20 per arm because (1) with 20 per arm, our 95% confidence intervals for key estimates (such as trial retention and intervention completion rates) will be narrow enough (<±20%) that, in terms of our criteria for progression to a definitive trial, there will be no substantive misclassification (‘red’ as ‘green’ or vice-versa; please see Table 2) and (2) at least 15 per arm is recommended for estimating variance to inform sample size requirements for a 90% powered main trial aiming to detect effects of moderate (clinically meaningful) magnitude [38]. Given service-activity data and prevalence of cognitive difficulties in people with MS, this target is achievable over a 12-month recruitment phase.

**Table 2 Tab2:** Feasibility assessment

Question	Data	Analysis	Progression criteria
Feasibility of the study	Interviews (i.e. post-trial feasibility interviews)—e.g. acceptability of randomisation; recommended changes to procedures	Framework analysis (structured, purposive coding of qualitative content)	Formative (included to support design of a definitive trial, but no assigned progression criteria cut-offs)
Acceptability of intervention	Drop-out rate (and reasons for withdrawal)	Frequencies/percentages	≥80% of SMART group complete ≥6 sessions (green), 79-60% complete ≥6 sessions (amber), <60% complete ≥6 sessions (red)
	Intervention progression and completion rates	Descriptive statistics/average percentage completion (and range)	Formative
	Interviews	Framework analysis	Formative
*Credibility* of intervention	Interviews (plus relevant comments within session recordings)	Framework analysis	Formative
Feasibility of measures	Missing response-data	Percentage	Formative
	Estimates of completion time	Descriptive statistics	Formative
	Late completion	Percentage	Formative
	Interviews	Framework analysis	Formative
Feasibility of framework for cost-effectiveness analysis	Missing data on intervention resource use	Percentage	Formative
	Missing response data—QALY measures and service and resource use questionnaire	Percentage	Formative

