	Estimates of time taken to complete measures - QALY measures and service and resource use questionnaire	Descriptive statistics	Formative
Feasibility of framework for cost-effectiveness analysis (cont…)	Late completion of measures—QALY measures and service and resource use questionnaire	Percentage	Formative
Feasibility of recruitment and randomisation	Numbers of outpatients eligible	Frequencies/percentages	Formative
	Numbers eligible who expressed interest/discussed w/researcher	Frequencies/percentages	Formative
	Numbers consenting/randomised	Frequencies/percentages	≥80% of planned (green), 79–60% of planned (amber), <60% of planned (red)
	Reasons for non-participation? (e.g. online modality as barrier? Unwilling to be randomised?)	Frequencies/percentages	Formative
	Interviews	Framework analysis	Formative
Feasibility of retention within the study	Number completing baseline and outcome assessments at Follow-up 1 (3 months)	Frequencies/percentages	≥80% completing to follow-up 1 (green), 79–-60% completing (amber), <60% completing (red)
Signal of efficacy	Indicative estimation of intervention effects	Estimates of (group-level) effect sizes with 95% CIs and proportions achieving reliable/clinically significant change	Red: 95% CIs exclude the possibility of a meaningful effect size for our screening measures (based on reliable-change criteria)

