### Recruitment

Participants will be recruited from MS clinics in two centres (Nottingham City and North Nottinghamshire). Recruitment will first be opened in the Nottingham site and, depending on the recruitment rates, we will secondarily open recruitment in the North Nottinghamshire site. The initial approach will be from a member of the patient’s usual care team (MS Nurses or Neurologists), and information about the trial will be on display in the relevant clinical areas.

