We will explain to the potential participant that entry into the trial is entirely voluntary and that their treatment and care will not be affected by their decision, and that they can withdraw at any time. In the event of their withdrawal, it will be explained that their data collected so far may not be erased in accordance with the University’s Research Privacy Notice and information given in the Participant Information Sheet and we will seek consent to use the data in the final analyses where appropriate. If participants withdraw from the study interventions, the study team will ask if they are willing to remain in the trial and complete trial assessments. As this is a feasibility study, recruitment will continue until at least 60 participants have been randomised (20 to each group).

Participants will not be paid to participate in the trial. Travel expenses will be offered for any visits in excess of usual care.

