### Randomisation and blinding

Participants will be individually randomised at baseline (after consent) in equal proportions to one of three groups (1:1:1 ratio) using block randomisation in permuted blocks of three and six.

Treatment allocation will be computer generated via the electronic trial database in Castor EDC (Castor Electronic Data Capture, available at: https://castoredc.com). Allocation sequence is concealed by Castor EDC until the randomisation of a participant. Castor EDC is used to assign participants to different groups.

Given the nature of the intervention, participants and the intervention-facilitating researchers will not be blinded. No unblinding procedures relating to potential adverse effects are therefore required. The assessments will be conducted by a Research Fellow who will be blind to treatment allocation. We will record any instances of unblinding to assess the feasibility of blinding outcome assessors to allocation.

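### The recruitment progression criterion has no period attached, so it is green by construction if the trial recruits to its stated stopping rule

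*Protocol article*

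**What the plan says.** Under recruitment and randomisation, Table 2 lists the data item "Numbers consenting/randomised". Its top tier is "≥80% of planned (green", and the full scale reads "≥80% of planned (green), 79–60% of planned (amber), <60% of planned (red". The row gives no period, no monthly rate and no number of sites.

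The Sample size section sets the stopping rule: "we will continue to approach and recruit people until we have randomised 60 participants (20 participants per arm". The text under Face-to-face invitation restates it: "recruitment will continue until at least 60 participants have been randomised (20 to each group". Allocation is "in equal proportions to one of three groups (1:1:1 ratio", which fits three arms of 20.

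A period appears once, at the end of the paragraph that sets the target: "this target is achievable over a 12-month recruitment phase". Neither the stopping rule nor the Table 2 row refers to it.

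The Recruitment section adds that, "depending on the recruitment rates, we will secondarily open recruitment in the North Nottinghamshire site". The Objective and Primary endpoints sections both name recruitment rates as something the study will assess.

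**The concern.** Two rules in the same document work against each other. One grades the final count against 60. The other keeps recruitment open until the count is 60. When the second is followed, the first returns its top grade whatever the speed of recruitment, so the grade reflects the stopping rule and not the data.

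This matters because the grade is meant to inform whether a definitive trial should go ahead. Only three rows of Table 2 carry a full green/amber/red scale: session completion, recruitment and retention. The retention row is tied to the 3-month follow-up, so the table can fix a timepoint where it chooses to. The recruitment row does not. The conditional second site adds to the problem: slow accrual may lead to more sites, and a bare count does not show that.

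**Working it through.** **Inputs from the protocol article**

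- Arms and size: 3 arms, 20 per arm (Sample size; Randomisation and blinding).
- Cut-offs: 80% and 60% of planned (Table 2).
- Recruitment phase: 12 months, stated as an expectation (Sample size).
- Monthly recruitment rate: not given. Every pace below other than the implied plan is an assumption.

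**Step 1. The planned number.** 3 × 20 = 60. This reproduces the stated target.

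**Step 2. Cut-offs as counts.** 0.80 × 60 = 48 and 0.60 × 60 = 36. Green is 48 or more, amber is 36 to 47, red is 35 or fewer.

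**Step 3. Grade under the stopping rule as written.** If recruitment ends when 60 are randomised, the graded percentage is 60/60 = 100%, at any positive pace. Only the time taken changes: months to target = 60 / pace.

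**Step 4. Grade at the protocol's own 12 months.** The implied plan is 60/12 = 5 per month. The cut-offs become 48/12 = 4 per month for green and 36/12 = 3 per month for the lower edge of amber. The expected percentage at month 12 is 12 × pace / 60.

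**Step 5. Would a 12-month window discriminate?** Take the 12-month count as Poisson with mean 12 × pace (an assumption), and read off the chance of 48 or more, 36 to 47, and 35 or fewer.

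| Assumed pace per month | Months to 60 | Grade as written | Expected % at month 12 | P(green) | P(amber) | P(red) |
|---|---|---|---|---|---|---|
| 2 | 30 | green | 40% | 0.000 | 0.013 | 0.987 |
| 2.5 | 24 | green | 50% | 0.001 | 0.156 | 0.843 |
| 3 | 20 | green | 60% | 0.032 | 0.490 | 0.478 |
| 4 | 15 | green | 80% | 0.519 | 0.450 | 0.031 |
| 5 (plan) | 12 | green | 100% | 0.951 | 0.049 | 0.000 |

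The as-written column is constant. The last three columns show that the same cut-offs, tied to 12 months, separate slow from adequate accrual: the chance of green rises from almost nil at 2.5 per month to 0.95 at the planned pace.

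**The case against.** A reader might infer that the criterion cannot fail under any circumstances. The document does not support that, for two reasons.

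- The paragraph that sets the target names a recruitment phase of 12 months. It is plausible to read the planned number as 60 within that phase, and the amber and red tiers make most sense on that reading. But the reader has to supply the link. The row does not make it, and the stopping rule is stated twice without a time limit.
- Under Auditing, the joint TSC/DMEC conducts an interim look at consent, retention and data completeness, and may recommend stopping. Recruitment could then end short of 60 and be graded amber or red. This is a real route, but it depends on a committee recommendation and sets no recruitment limit.

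A reader might also infer that the study will learn nothing about recruitment. That is not so. Recruitment rates are an objective and a primary endpoint, the Data-Analysis section plans to describe them, and Table 2 collects numbers eligible, numbers interested and reasons for non-participation. A trial that took 24 months would show this in its report. This part of the objection stands and limits the harm to the rating itself.

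A third tempting reading is that screen failures would count towards green, because the data item joins consenting and randomised, and Table 1 places consent at Screen 1, before the SDMT at Screen 2. The only planned number is 60 randomised, so the percentage most naturally applies to those randomised. The wording is loose, but the document does not show that consenters would be graded.

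Finally, the article condenses a fuller protocol that is not shown and that may give recruitment dates. That tempers confidence that no limit exists anywhere. It does not remove the mismatch between two rules that this text states in full.

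**Conclusion.** The point holds in conditional form: if the trial runs to its stated stopping rule, the recruitment criterion is met by construction and its grade carries no information about pace. This is a mismatch between two stated rules, not a detail left to another document.

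Its size can be shown only by illustration, because the article gives no recruitment rate. At an assumed 2.5 per month, the same accrual is 50% of planned and red at month 12, and 100% and green at month 24. The Poisson probabilities also rest on assumed rates. The cut-offs of 48 and 36 and the planned 5 per month follow directly from the article's own figures.

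The target of 60 is not in question, and the estimation of effects is untouched. The change should be made, but it is not critical.

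**What to change.** In the recruitment row of Table 2, define the criterion as the number randomised within 12 months of opening recruitment, as a percentage of 60: green at 48 or more, amber at 36 to 47, red below 36. State that the rating is fixed at month 12 even if recruitment then continues to 60 for precision, and align the two statements of the stopping rule with this. Name randomised participants as the count that is graded, and report consenters separately. State the number of sites open during the window; a rate per site-month would be a useful addition, since the second site opens conditionally.

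The cost is one line in the table and small wording changes in two sections. It uses only the article's own 60, 12 months, 80% and 60%. The downside is that the rating may be less favourable. The window should be set before accrual is graded, because choosing it afterwards would be post hoc.

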### Recruitment

Participants will be recruited from MS clinics in two centres (Nottingham City and North Nottinghamshire). Recruitment will first be opened in the Nottingham site and, depending on the recruitment rates, we will secondarily open recruitment in the North Nottinghamshire site. The initial approach will be from a member of the patient’s usual care team (MS Nurses or Neurologists), and information about the trial will be on display in the relevant clinical areas.

#### Postal invitation

In the recruiting MS clinics, the clinical teams have regular contact with all people diagnosed with MS in the community. The clinical staff will identify potential participants from hospital records. An invitation letter and Participant Information Sheet (PIS) will be sent to identified patients via post or email by the MS Nurses or a member of the clinical team. This invitation letter will include study information and research team details. Patients who are interested will contact the research team—whereupon a researcher will address any questions, ensure their understanding of the study, and arrange screening procedures. The researcher will explain that the screening procedures are to check that the patient meets the study inclusion criteria.

#### Face-to-face invitation

In addition to the invitation letter, potential participants who attend clinic visits can be introduced to the study by their neurologist or MS nurses and given/sent the PIS. People who do not contact the research team will have a single phone call by the clinical team to enquire whether they remember receiving the PIS and whether they would like further information about the study, where possible. If they do not wish to have further information, no further contact will be made by the researchers. If, however, they wish to have more information, the clinical team will request verbal consent to pass on their contact details to a researcher, who can provide them with more information about the trial. The clinical team will record the date and time when verbal consent was obtained to pass on contact details. The research team will then contact potential participants to address any questions, ensure their understanding of the study, and enquire whether they are still interested in taking part. If so, screening procedures will be arranged—the researcher will explain that the screening procedures are to check that the patient meets inclusion criteria.

Screening appointments will be arranged as suitable to the potential participant: The first screening procedure (completion of PDQ and demographic information) can be undertaken via an online survey platform or via telephone/video call with a researcher; the second screening procedure (completion of RBANS) must be undertaken with a researcher either via video call or in-person. Potential participants will be sent a Consent Form (CF) and (if requested) another copy of the PIS in advance of the first screening appointment so that they have sufficient time and information to understand the study before consenting to the study and engaging in screening procedures.

We will explain to the potential participant that entry into the trial is entirely voluntary and that their treatment and care will not be affected by their decision, and that they can withdraw at any time. In the event of their withdrawal, it will be explained that their data collected so far may not be erased in accordance with the University’s Research Privacy Notice and information given in the Participant Information Sheet and we will seek consent to use the data in the final analyses where appropriate. If participants withdraw from the study interventions, the study team will ask if they are willing to remain in the trial and complete trial assessments. As this is a feasibility study, recruitment will continue until at least 60 participants have been randomised (20 to each group).

Participants will not be paid to participate in the trial. Travel expenses will be offered for any visits in excess of usual care.

### Randomisation and blinding

Participants will be individually randomised at baseline (after consent) in equal proportions to one of three groups (1:1:1 ratio) using block randomisation in permuted blocks of three and six.

Treatment allocation will be computer generated via the electronic trial database in Castor EDC (Castor Electronic Data Capture, available at: https://castoredc.com). Allocation sequence is concealed by Castor EDC until the randomisation of a participant. Castor EDC is used to assign participants to different groups.

Given the nature of the intervention, participants and the intervention-facilitating researchers will not be blinded. No unblinding procedures relating to potential adverse effects are therefore required. The assessments will be conducted by a Research Fellow who will be blind to treatment allocation. We will record any instances of unblinding to assess the feasibility of blinding outcome assessors to allocation.

### Data collection methods

#### Screening and baseline measures

PDQ [39]: to assess self-reported cognition (for screening and focal outcome measurement). Perceived cognitive function, measured using the 20-item PDQ, assesses cognitive functions most affected in MS: attention, memory, planning, and organisation. The PDQ is associated with objective cognitive performance in MS [40] and has shown excellent internal consistency (*ɑ* = .93) [39]. We will use a cut-off of ≥27 [41] to identify study eligibility (i.e. 1.5 SDs or more above the normative mean).

*Symbol Digit Modalities Test (SDMT)* [42]: to assess objective cognitive performance (processing speed; for screening and focal outcome measurement). The SDMT [42] is a symbol substitution test that examines processing speed and attention and is reported as the most sensitive test for MS cognitive problems [43]. The SDMT has shown excellent test-retest reliability (*r* = .97) [43]. Age-, education-, and gender-adjusted norms are available [44], and these will be used to define cognitive impairment (for study eligibility) as scoring 1.5 SDs or more below the normative reference value.

The RBANS [45]: to further assess objective cognitive performance (attention, language, visuospatial/constructional abilities, and immediate and delayed memory; for screening and focal outcome measurement). The RBANS is a brief test of cognitive abilities across multiple domains, with domain composite scores derived from 12 subtests (list learning, story memory, figure copy, line orientation, picture naming, semantic fluency, digit span, coding, list recall, list recognition, story recall, figure recall). Subtests also support the derivation of an executive errors scale (reflecting executive functioning) [46]. Normative data provide age- and education-corrected scores [47] and these can be used to further define cognitive impairment as scoring ≥1 SD below the mean on ≥1 RBANS- composite [48]. The RBANS is validated in this population and has various strengths (including alternate forms to enable repeated assessment) [49]; adequate test-retest reliabilities have been found across subtests (with *r* = .80 for the Total Scale) [50].

*Generalized Anxiety Disorder Scale-7 (GAD-*7) [51] *and Patient Health Questionnaire-9* (PHQ-9) [52] to assess distress—an important correlate of cognitive concerns. The GAD-7 and PHQ-9 have been shown to retain construct validity and acceptable internal consistencies for use in MS (*ɑ*s = .75 and .82, respectively) [53, 54]. In this population, scores ≥10 in either anxiety or depression indicate clinical distress [55]

*Modified Fatigue Impact Scale–5-Item (MFIS*-5) [56]: to assess fatigue and its perceived impact on cognitive, physical, and psychosocial functioning. The MFIS-5 has demonstrated excellent internal consistency (*ɑ* = .90) and construct validity [57] and will be applied to identify possible fatiguing effects of the intervention.

*Personal Questionnaire* (PQ) [58]: to assess patient-described cognitive problems and their everyday impact (patient-generated outcome measure). The PQ has demonstrated good internal consistency (*ɑ* = .80) and treatment sensitivity [58].

EQ-5D-5L [59, 60]: provides health state utility values (HSUVs) and is NICE recommended for estimating the cost-per-QALY of interventions [61] (informing cost-effectiveness framework). The EQ-5D-5L has demonstrated good test-retest reliability (ICC = .80) and construct validity in people with MS [62].

*MS Impact Scale–29* (MSIS-8D; v.2): MS-specific QoL to additionally provide MS-specific HSUVs [63, 64] (informing cost-effectiveness framework); this scale has shown good internal consistency (*ɑ*s = .80) and treatment sensitivity [65].

ICECAP-A [66]: Provides capability wellbeing values (reflecting the ability to ‘do’ and ‘be’ the things that are important in life) and is NICE recommended for use in economic evaluations, alongside health measures [67] (informing cost-effectiveness framework). The ICECAP-A has been shown to have acceptable internal consistency (*ɑ* = .74) and construct validity [68].

*Service- and resource-use questionnaire* developed from our previous pilot work (informing cost-effectiveness framework). The questionnaire design has been informed by the Database of Instruments for Resource Use Measurement (DIRUM) [69] and the core resource-use items [70].

These measures were selected because they have adequate psychometric properties, have been used in other trials with this population, are brief, and capture the outcomes our PPI group felt were most important for people with MS.

#### Follow-up measures

All participants will be assessed 3 and 6 months post-randomisation, using the same measures as at baseline. The assessing Research Fellow will be blind to allocation (any instances of unblinding will be recorded).

#### Intervention resource requirements

The resources needed to deliver the intervention (e.g. providing the SMART programme online for people with MS, facilitators’ time) will be assessed via participant case records and discussion with the intervention developers.

